## Abstract

**Background:**

Tobacco use is one of the most common preventable causes of death, but more than half of the Chinese men still use tobacco products. Moreover, 63.6% of Chinese smokers have stated that they would not consider quitting. Specialized and intensive smoking-cessation services are too expensive and passive to have major clinical and public health impacts in developing countries like China. Smoking cessation medications are not covered by medical insurance, and their high price prevents Chinese smokers from using them. Brief interventions are needed to provide cost-effective and timesaving tobacco dependence treatments in China mainland.

**Methods/design:**

We describe a two-arm randomized controlled trial for smokers who have no intention to quit. The project will be conducted in outpatient clinics at a large hospital in Beijing, China. Both arms include one face-to-face interview plus five follow-up interventions. Each intervention will last approximately one minute. Subjects allocated to the smoking-reduction intervention arm (SRI) will be advised to reduce smoking consumption to at least half of their current consumption level within the next month. All subjects in the SRI will be warned to bear in mind that an attempt to reduce smoking is an intermediate step before complete cessation. Smokers who have successfully reduced their smoking consumption will be encouraged to completely cease smoking. Controls are subjects allocated to the exercise- and diet-advice arm (EDA) and will be given advice about healthy diet and physical activity, but the advice will not include smoking cessation or reduction. Data collection will be done at baseline and at each follow-up interview using standardized questionnaires. The primary outcomes include self-reported and biochemically verified 7-day point prevalence and prolonged abstinence rates at 12-month follow-up.

**Discussion:**

We expect that an intention to quit in smoking outpatients can be motivated by physicians in the clinic setting. If this very brief smoking-reduction intervention can be demonstrated to have a positive impact on long-term smoking cessation, this strategy has the potential to be a viable and acceptable approach and may be used widely in China and elsewhere.

**Clinical trial registration:**

ClinicalTrials.gov: NCT02370147 (date of registration: 23th February, 2015).

## Background

Tobacco use is one of the most common preventable causes of death, and many countries are expending effort to reduce the smoking prevalence. However, the prevalence of smoking in China has declined little in recent years. The Global Adult Survey reported that the prevalence of smoking among Chinese men decreased from 57.4% in 2002 to 52.9% in 2010 [1,2]; thus, more than half of Chinese men are still current smokers. Although quitting can reduce the mortality due to smoking-induced diseases, 63.6% of Chinese smokers would not consider quitting [2]. Therefore, it is critical to expand smoking prevention and cessation efforts in China.

In developed countries and regions, including Hong Kong and Taiwan with mostly Chinese [3-6], smoking cessation services, such as smoking cessation clinics and telephone quitlines, are well established. These services play an important role in public health. However, these specialized and intensive smoking-cessation services are too expensive and passive to have major clinical and public health impacts in developing countries like China, as they require continuous and enormous funding and intensive training for counselors, and involve other costs, such as pharmacotherapy. Pharmacotherapy is an effective treatment modality for tobacco dependence, but it is not widely used in China mainland [7,8]. One of the most important reasons why pharmacotherapy is not widely used for smoking cessation is that smoking-cessation medications are not covered by medical insurance, and they are too expensive. Hence, there is an urgent need for a much cheaper yet effective strategy for helping smokers to quit.

In general, commonly used behavioral intervention categories fall into two categories: brief or minimal interventions and intensive interventions [9]. A brief or minimal intervention was defined in a Cochrane review as less than 20 minutes of advice plus up to one follow-up session [10]; other interventions were defined as intensive. Stead et al. reported that the quit rate following brief advice from physicians was significantly higher than that following no advice (or usual care); the relative risk (RR) was 1.66, and the 95% confidence interval (CI) was 1.42 to 1.94 [10]. However, the quit rates following intensive counseling were not found to be significantly different from those following brief counseling in two Cochrane reviews [10,11]. As a result, brief behavioral interventions are recommended to address the need for cost-effective and timesaving interventions for smokers [12]. In 2013, Lin et al. reported that their pilot randomized controlled trial in Guangzhou, China showed that a 30-second smoking cessation intervention by a physician was an effective way to encourage smokers to quit; the 12-month continuous abstinence rate was 14.9%, compared with 3.8% in the control group. These results suggest that a very brief intervention can achieve a measurable effect in China mainland [13,14].

For smokers who have no intention to quit, smoking-reduction interventions may be a therapeutic choice [15,16]. The common definition of successful smoking reduction is a self-reported reduction of daily cigarette consumption by 50% or more compared with baseline [17]. However, smoking-reduction treatment has been highly controversial in the past [18,19]. The main concerns and uncertainties regarding this approach were that (a) a short-term reduction may not be maintained for long periods [20]; (b) smoking reduction does not necessarily imply harm reduction [21-23]; and (c) future attempts to quit smoking may be undermined by short-term reductions in daily cigarette consumption [20]. However, according to a meta-analysis by Asfar et al., pharmacological combined with smoking-reduction interventions significantly increased long-term smoking cessation rates by factors of 2.14 [19]. Recently, a randomized controlled trial by Chan et al. also supported this conclusion [24]. It has been reported that a smoking-reduction approach may be more likely to be adopted by a broader range of smokers than traditional smoking-cessation interventions [25]. However, limited evidence exists about the effectiveness of behavioral smoking-reduction randomized controlled trials for smokers who have no intention to quit. Glasgow et al. implemented an individual behavioral smoking-reduction intervention for smokers who were not interested in quitting smoking, and the results favored the intervention but did not reach statistical significance [26]. To our knowledge, no previous study has investigated whether a very brief smoking-reduction intervention can increase quitting rates in China; whether this approach is feasible and effective for increasing long-term quit rates among smokers who have no intention to quit remains unclear.

Brief interventions are needed to provide cost-effective and timesaving treatments for tobacco dependence, particularly in developing countries like China. The protocol described here is designed to fit the real life conditions of China mainland. Smoking information should be routinely collected from outpatients in clinics; this interaction provides a good opportunity for doctors to persuade outpatients and their companions to quit smoking. A very brief (i.e., approximately one-minute) smoking-reduction intervention will be proposed to smokers who have no intention to quit. All smokers receiving such intervention will be asked to bear in mind that an attempt to reduce smoking is an intermediate step before complete cessation. During follow-up interviews, if smokers have already reduced their tobacco consumption, they will be encouraged to quit smoking during follow-up interviews. This very brief, active and minimal cost individual smoking reduction intervention will provide strong evidence for a new approach for treating tobacco dependence in China mainland and elsewhere.

## Methods/Design

### Study design

In the present protocol, we describe a two-arm randomized controlled trial for smokers who have no intention to quit.

### Participants, setting and procedure

The project will be conducted in the outpatient clinics of the People's Liberation Army General Hospital in Beijing, China. Physicians in outpatient clinics in the endocrinology and acupuncture departments will be asked if they want to participate in the trial. Those who agree to participate will be recruited into the current project. Before the trial starts, the participating physicians will be trained. Most of the physicians are in busy clinical settings, and they may not be able to afford the extra few minutes needed to advise each smoker to quit [14]; therefore, students of the physicians will also be trained to assist with completing the interviews.

Current smokers who are outpatients attending the clinics and their companions will be included in the project. Each self-reported smoker will be asked, “Do you have an intention to quit smoking?” Smokers who answer that they are “beginning to quit within the next 7 days” or “within 30 days” will be excluded from the trial. Smokers who answer that they intend to quit “in the next 6 months” or “after 6 months” or that “I’m not making a decision about quitting smoking” will be included in the trial [27,28].

Participants will be eligible for the study if they meet the following criteria: (1) aged ≥18 years; (2) have smoked ≥10 cigarettes per day in the past month; (3) have no intention to quit smoking; (4) agree to offer their telephone numbers and sign informed consent forms for participation.

Participants will be excluded from the study if they meet the following criteria: (1) have smoked fewer than 10 cigarettes per day in the past month; (2) have a disease that makes a physician think it would be unethical not to advise a patient to quit smoking as soon as possible; (3) are cognitively or otherwise impaired (i.e., deaf or unable to understand and complete a questionnaire reliably); (4) are pregnant or lactating females.

Signed, informed consent will be obtained from all eligible participants. Information about the project aims, interventions, assessments and data collection will be included on a paper form. Eligible participants will also be asked for a telephone number for follow-up interviews.

The study has been approved by the Independent Ethics Committee of the Chinese People's Liberation Army General Hospital.

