### Randomization

Before participant recruitment, a research assistant on the project will generate random numbers for group assignments using a computer. If an individual is eligible to participate in the study, and written consent is obtained, trained counselors will randomly allocate the participant to a treatment group by opening a serially labeled, opaque and sealed envelope, and a card inside will indicate the group to which the participant should be randomly allocated.

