### Sample-size calculation

Because no similar studies have previously been conducted in China mainland, the effect-size estimation is based on results from Hong Kong [14,24]. We assume that the quit rate at the 12-month follow-up of the SRI group would be 15% versus 5% for the control group. To detect a difference of 10%, it is estimated that 138 subjects would be needed for each group given an alpha level of 5% (two-sided) and a statistical power of 80%. A total of 331 participants will be recruited based on a possible loss of 20% of the participants at the 12-month follow-up.

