### Smoking-reduction intervention group (SRI)

In the first face-to-face interview, trained counselors will give each smoker a very brief smoking-reduction intervention lasting approximately one minute. Smokers will be warned that many non-communicable diseases are caused by smoking, such as cancer, coronary heart disease, respiratory diseases and many other health problems. Moreover, one out of two smokers will be killed by smoking [31]. Smokers will be advised to reduce smoking consumption to at least half of their total consumption within the next month. Finally, all smokers will be asked to bear in mind that the current attempt to reduce smoking would be an intermediate step before complete cessation.

The tobacco-use status of each smoker will be assessed by another trained counselor who will not know the aim of the project at 1 week and 1, 3, 6 and 12 months via telephone follow-ups. Additional smoking cessation interventions will be given at each follow-up according to their updated smoking status. Smokers will be encouraged to reduce their smoking consumption if they have not changed their smoking status, and smokers who have successfully reduced their smoking consumption will be encouraged to quit completely; smokers who have successfully quit smoking will be supported to maintain abstinence. Each follow-up will last for about one minute.

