### Exercise- and diet-advice group (EDA, Controls)

In the first face-to-face interview, trained counselors will give each smoker very brief advice for about one minute. Smokers will be advised to engage in regular physical activity three or four times per week and to have a healthy and balanced diet including more fruits and vegetables, which are rich in vitamins, high in nutrition values and yet low in calories.

The tobacco-use status of each smoker will be assessed at each follow-up interview, similar to the SRI group. Smokers will be advised to engage in regular physical activity and to eat more fruits and vegetables. Each follow-up will last approximately one minute. Throughout the process, smoking cessation or smoking reduction will not be mentioned.

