### Data analysis

Epidata (3.1) will be used to perform double entry of the collected data. We will use SPSS (IBM Corp. Armonk, NY, USA) for Windows (version 19.0) for data analysis. Baseline characteristics will be compared using chi-squared tests, Mann-Whitney tests and t tests. Regression models will be used to compare the outcomes of different interventions. We will adjust for baseline differences by including the variables in the regression models if necessary. Smokers who cannot be contacted during follow-up will be considered non-quitters or non-reducers in an intention-to-treat (ITT) analysis. For sensitivity analysis, subjects lost to follow-up will be excluded for per protocol (PP) sensitivity analyses.

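### An outpatient and their companion can both enrol and are randomised separately, so a pair can be split across arms and the control exposed to the smoking-reduction advice

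*Protocol article*

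**What the plan says.** All references are to the protocol article.

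- **Participants, setting and procedure:** "Current smokers who are outpatients attending the clinics and their companions will be included in the project". None of the four inclusion or four exclusion criteria restricts entry to one smoker per patient-companion party.
- **Randomization:** once an individual is eligible and has consented, "trained counselors will randomly allocate the participant to a treatment group by opening a serially labeled, opaque and sealed envelope". No exception is made for people who attend together.
- **Smoking-reduction intervention group (SRI):** "Smokers will be advised to reduce smoking consumption to at least half of their total consumption within the next month". Participants are told that this is a step towards stopping completely, and the advice is renewed at five telephone follow-ups over 12 months.
- **Exercise- and diet-advice group (EDA, Controls):** "Throughout the process, smoking cessation or smoking reduction will not be mentioned".
- **Sample-size calculation:** "We assume that the quit rate at the 12-month follow-up of the SRI group would be 15% versus 5% for the control group", and from this "it is estimated that 138 subjects would be needed for each group" at two-sided 5% alpha and 80% power.
- **Data analysis:** "Regression models will be used to compare the outcomes of different interventions". The text says nothing about pairs in either direction.

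**The concern.** The control condition is defined by silence about reducing or stopping smoking. The active treatment is about a minute of spoken advice, which one person can easily repeat to another. Subjects are not blinded. A relative or friend who attended the same clinic visit is an obvious route for that advice to reach a control, and the control can also watch the partner's attempt.

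Any such spill-over raises the quit rate in the control arm and understates the effect of the intervention. The sample size is calculated for the full 10-point contrast and holds no reserve for this. Who may enrol and what unit is allocated are design choices that the article itself fixes, and a later analysis plan cannot remove contamination once pairs have been split.

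**Working it through.** **1. The plan's own figure.** Inputs from Sample-size calculation: 15% and 5%, two-sided alpha 5%, power 80%. The unpooled two-proportion formula gives

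n = (1.960 + 0.842)² × [0.15 × 0.85 + 0.05 × 0.95] / 0.10² = 137.4, rounded up to 138 per arm.

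This reproduces the stated 138. The power at 138 per arm by the same formula is 80.2%. The calculation assumes independent subjects and no contamination.

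**2. How many controls are exposed.** Let f be the share of participants who belong to an enrolled pair. With 1:1 individual allocation, about half of the pairs are split, so about f/2 of the controls have a partner in the SRI arm.

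**3. Diluted contrast.** Let c be the fraction of the 10-point effect that such a control gains. Then

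control rate = 5% + (f/2) × c × 10 points.

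Example with f = 20% and c = 50%: 5% + 0.10 × 0.5 × 10 = 5.5%, a difference of 9.5 points. Standard error at 138 per arm = √[(0.15 × 0.85 + 0.055 × 0.945)/138] = 0.0361. Power = Φ(0.095/0.0361 − 1.960) = 75.0%.

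Neither f nor c is in the documents. Both are assumptions, so a range is shown:

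| In pairs (f) | Spill-over (c) | Control rate | Power at 138 per arm | Per arm for 80% |
|---|---|---|---|---|
| 0% | – | 5.0% | 80.2% | 138 |
| 10% | 25% | 5.125% | 78.9% | 142 |
| 10% | 50% | 5.25% | 77.7% | 147 |
| 20% | 25% | 5.25% | 77.7% | 147 |
| 20% | 50% | 5.5% | 75.0% | 157 |
| 30% | 50% | 5.75% | 72.2% | 167 |

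**4. Does ignoring the pairing distort the test?** Under individual randomisation, a positively correlated pair in the same arm adds to the variance of the difference, and a split pair subtracts from it. With about half of each, the two cancel. A simulation confirms this. It used 276 subjects, a 10% event rate in both arms, a two-proportion test that ignores pairing, and 20,000 runs per setting. With 20–100% of participants in pairs and a within-pair correlation of 0.3–0.5, type I error was 4.8–5.1%.

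**5. The same test if pairs were allocated together.** The offset disappears. If pairing were still ignored, type I error would be 5.6–5.8% with 20% in pairs and 6.9–7.7% with 50%. The design effect is about 1 + f × ρ, where ρ is the within-pair correlation:

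- f = 10%, ρ = 0.1: 1.01, or 139 per arm.
- f = 30%, ρ = 0.3: 1.09, or 150 per arm.

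**The case against.** **Pairs may be rare.** The article does not say how often both members of a party will enter. Each must smoke at least 10 cigarettes a day, have no plan to quit within 30 days, pass the exclusions and consent. The only smoking prevalence given is 52.9% in men (Background). If the other member of the party smokes at that rate, a 20% pair share needs about 0.20/0.529 = 38% of participants to attend with a man, and every one of those who smokes to be eligible and to enrol. A 40% share needs 0.40/0.529 = 76%. Smoking may run in households, which would ease this, but the documents do not say so. This objection stands: the larger power losses should not be presented as expected.

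**Spill-over may be small.** A second-hand account is not the counsellor's advice plus five follow-ups tailored to smoking status. Spill-over of 50% would lift an exposed control from 5% to 10%. This also stands, and is why 25% is shown beside it.

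**Controls are not naive in any case.** The consent form covers the project's aims and interventions, and tobacco use is asked about at every follow-up. So a split pair adds to the exposure of some controls. It does not by itself undo the control condition.

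**A stronger reading.** A reader might infer that paired outcomes are analysed as independent and that the standard error is therefore wrong. The documents do not support this. Data analysis names only regression models and no variance method, and the full protocol and analysis plan are not shown. Step 4 of the working also shows that, with individual allocation, ignoring pairing leaves type I error at about 5%.

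None of this answers the design point: the stated enrolment and allocation rules permit split pairs, and nothing prevents them.

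**Conclusion.** The point holds as one of contamination. Followed as written, the protocol can place two people who attend together in opposite arms, and so expose a control to the advice that the control arm is meant to leave out. The bias is towards no difference. It costs power and understates the effect, but does not create a false positive.

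The loss is modest under moderate assumptions: power of about 79–78% with 10% of participants in pairs and 25–50% spill-over, and about 75% with 20% in pairs and 50% spill-over. These figures rest on an assumed pair share, an assumed spill-over and an even split of pairs. If pairs are rare, the loss is negligible. The change is worth making because it is cheap, not because the trial is shown to be seriously underpowered on this account.

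**What to change.** **Preferred:** randomise at most one smoker per patient-companion party, and fix before allocation which one that is. The stated analysis and sample-size method need no change. The cost is slightly slower recruitment.

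**Alternative:** allocate the whole party with one envelope.

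- Obtain consent from every smoker in the party before the envelope is opened. Otherwise the second person would decide on consent with the arm already known.
- Record a party number.
- Use GEE or cluster-robust standard errors by party in the outcome regressions. Under this option the clustering does matter (step 5 of the working).
- Allow for a design effect of about 1 + pair share × within-pair correlation, for example 1.01–1.09, or 139–150 evaluable subjects per arm instead of 138.

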## Discussion

The current protocol describes a two-arm randomized controlled trial. We aim to test the long-term (1 year) effectiveness of a very brief behavioral smoking reduction intervention on smokers who have no intention to quit.

Previous studies have used various definitions and time frames to define an intention to quit, such as ‘not willing to quit in the next four weeks’ [24], “uninterested in quitting at that time” [26], “no intention to quit within the next month” [33] or “not ready to quit” [34]. In the current trial, we use a recognized theory that incorporates a stage-of-change model (include pre-contemplation, contemplation, preparation, action and maintenance) [19,27,28]. We define pre-contemplators (will quit after 6 months or undecided about quitting) and contemplators (will quit in the next 6 months) as “having no intention to quit.”

While it has been reported that few smokers have an intention to quit in China [35], physicians should play an important role in smoking cessation [36,37]. Physicians have a good opportunity to advise outpatients when they visit their clinics. We expect that more outpatients can be motivated to quit by physicians in clinic settings. Traditional smoking-cessation services often focus on smokers who express an interest in quitting. Clearly, it will be more effective for physicians to offer assistance to all smokers, not only to those selected by motivation [38]. Different methods of intervention should be used for smokers with different smoking histories. If a very brief smoking-reduction intervention is demonstrated to have a positive impact on long-term smoking cessation, this strategy has the potential to be a viable and acceptable approach that could be used widely in China and elsewhere.

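### The population labelled as having no intention to quit includes smokers who plan to quit within follow-up; the label needs its 30-day window and the result needs reporting by stage

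*Protocol article*

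**What the plan says.** Participants, setting and procedure sorts smokers by their answer to a question about intention to quit. One group is turned away: "Smokers who answer that they are “beginning to quit within the next 7 days” or “within 30 days” will be excluded from the trial". Three answers qualify. Two state a plan: "Smokers who answer that they intend to quit “in the next 6 months” or “after 6 months". The third is that no decision has been made.

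The same section then lists as an eligibility criterion: "3) have no intention to quit smoking". It gives no time window. The unqualified label also appears in the Abstract (Methods/design), in Study design, in Description of the intervention and in the opening aim of the Discussion. Description of the intervention says that smokers with an intention to quit are advised to stop at once, and that those without one are randomised.

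The Discussion later gives the operational meaning of the label, based on a stage-of-change model: "We define pre-contemplators (will quit after 6 months or undecided about quitting) and contemplators (will quit in the next 6 months) as". The term being defined there is the same bare label. Among the earlier definitions it reviews is one that keeps its window: "no intention to quit within the next month".

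The Background motivates the trial with the figure that "63.6% of Chinese smokers would not consider quitting". The primary outcomes are abstinence rates at 12 months.

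**The concern.** The label and the rule describe different people. A smoker who answers that he will quit in the next 6 months fails the eligibility criterion as worded and belongs, by the wording of Description of the intervention, with those advised to quit at once. The screening rule nevertheless enrols him, and his own planned quit date comes before the endpoint.

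What is at stake is what the trial may claim. The rationale is about smokers whom ordinary cessation services do not reach because they show no interest in quitting. If much of the effect arises in smokers who already planned to quit during the year, a conclusion worded with the bare label would credit the intervention with an effect in a group where it may be smaller or absent. The pooled result alone cannot tell these cases apart.

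**Working it through.** **1. The passages side by side**

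| Screening answer | Stage in the Discussion | Enrolled? | Planned quit date inside 12 months? |
|---|---|---|---|
| Within 7 days or 30 days | not among the enrolled stages | no | yes |
| Next 6 months | contemplator | yes | yes, always |
| After 6 months | pre-contemplator | yes | possibly |
| No decision | pre-contemplator | yes | none stated |

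The screening rule and the Discussion's definition agree with each other. The unqualified label agrees with neither. A label that fits the rule is: no intention to quit within 30 days.

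**2. The plan's own figure**

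Inputs from Sample-size calculation: 15% versus 5%, two-sided alpha 5%, power 80%, 138 per group. With unpooled variance:

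n = (1.960 + 0.842)² × (0.15×0.85 + 0.05×0.95) / 0.10² = 137.4, rounded up to 138.

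The figure is reproduced and does not depend on the stage mix.

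**3. What the pooled result can hide**

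The article gives neither the share of contemplators nor quit rates by stage. The values below are assumptions.

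*Share of control quitters.* Let contemplators be a share p of the sample and quit r times as often as the rest. Their share of control quitters is p·r / (p·r + 1 − p).
- p = 0.3, r = 2: 0.6/1.3 = 46%
- p = 0.3, r = 4: 1.2/1.9 = 63%
- p = 0.5, r = 2: 1.0/1.5 = 67%
- p = 0.5, r = 4: 2.0/2.5 = 80%

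This describes who quits in the control arm. It is not a share of the treatment effect.

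*Effect in contemplators only.* Suppose everyone else quits at 5% in both arms. For 15% versus 5% overall, the intervention-arm rate in contemplators must be 0.05 + 0.10/p.
- p = 0.10: 105%, impossible
- p = 0.25: 45%
- p = 0.50: 25%
- p = 0.75: 18%

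*Effect in both groups.* Take p = 0.5, with contemplators at 24% versus 8% and the rest at 6% versus 2%. Overall this is (24 + 6)/2 = 15% versus (8 + 2)/2 = 5%. The differences are 16 and 4 points, but the risk ratio is 3 in both groups.

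The same planned result therefore fits no effect outside contemplators, or a tripling of quitting there. Only results by stage separate the two.

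**4. How precise stage results would be**

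Power for non-contemplators alone at 15% versus 5% is taken as Φ{[0.10 − 1.96·√(2×0.10×0.90/n)] / √(0.175/n)}, where 0.175 = 0.15×0.85 + 0.05×0.95 and n = 138(1 − p) per arm. With all 138 per arm this gives 79.4%.

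| Contemplator share p | n per arm, others | Power |
|---|---|---|
| 0.10 | 124.2 | 75% |
| 0.25 | 103.5 | 67% |
| 0.50 | 69 | 50% |
| 0.75 | 34.5 | 28% |

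At p = 0.5 the 95% half-width of the difference is 1.96 × √(0.175/69) = 9.9 points, against 1.96 × √(0.175/138) = 7.0 points in the whole sample.

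**The case against.** The strongest reply is that this is a disclosed design choice. The Discussion reviews earlier definitions, names its model and states the rule, and screening follows it. Windows of about a month have precedent in the studies it lists. Smokers who would have quit anyway are randomised to both arms, so they create no difference between arms. All of this stands.

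Four stronger readings are tempting, and the document does not support them.

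- A reader might infer that the 12-month result cannot answer the trial's question. It can, for the population that the Discussion defines.
- A reader might take the 16- versus 4-point split as showing that the intended group gains little. That split is a constant risk ratio of 3 on assumed rates. At a 25% share, a result carried by contemplators alone needs a 45% quit rate among them.
- A reader might conclude that outright refusers are missed because no listed answer is a refusal. Nothing excludes a smoker who says no. The criterion admits him, and the answer list comes from a condensed article.
- A reader might want every claim about smokers with no intention to quit restricted to pre-contemplators. That group includes those who will quit after 6 months, so the restriction would not isolate smokers without an intention.

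It is also fair to say that analysis by stage may stand in an analysis plan that is not shown, and that the secondary outcome on predictors of quitting could include stage. Its absence from the article is therefore not the fault. The fault is the conflict between the label and the rule, which this document shows by itself.

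**Conclusion.** The point holds as one about the scope of the conclusion. The bare label conflicts with the screening rule, and the disclosed definition makes the conflict traceable without removing it: to call "contemplators (will quit in the next 6 months) as “having no intention to quit" is to use the words against their ordinary sense. Readers of the abstract and aim meet only the label.

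Internal validity and the sample size of 138 per group are untouched. The size of the problem depends on the unreported stage mix and on stage-specific quit rates. The figures of 46% to 80% and 25% versus 5% illustrate a range of assumptions and are not estimates for this trial. With few contemplators the matter is small: at a 10% share they could not produce the planned result alone. With half or more they could do so at rates of 25% or less.

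**What to change.** 1. State the population as smokers with no intention to quit within 30 days in the aim, in criterion (3), in Description of the intervention and in the conclusions. Use the same wording in the Abstract and Study design, so that the sections agree with the screening rule.
2. Carry the screening answer (next 6 months, after 6 months, undecided) into the baseline data and include it as a prespecified covariate in the primary regression.
3. Report 12-month quit rates by arm, and the arm difference with a confidence interval, separately for contemplators and pre-contemplators. Present these as estimates and not as powered tests.

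The cost is a change of wording, one covariate and one table from an answer already obtained at screening. No change in sample size is needed. The price is a narrower headline claim and stage-specific estimates that will be imprecise, as the half-width of about 10 points at an even split shows.
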